### Criteria for discontinuing or modifying allocated interventions {11b}

No modification of the interventions is anticipated throughout the trial. Reasons for discontinuation of study intervention include:*Cognitive impairment*: If the study participant demonstrates difficulty following or remembering study tasks, a member of the study team may repeat the SPMSQ. If a participant is identified as potentially having cognitive impairment, as assessed by the SPMSQ, and four or more errors are recorded, the study staff will notify the PI to discuss the participant’s cognitive state. The study staff will also send a letter to the participant’s neurologist to inform them that a potential decline in cognition has been observed with a recommendation to evaluate the participant’s cognition and competence as they deem appropriate. The neurologist will be informed if more than four errors were documented, which is a medical stop point. If the neurologist determines that the participant is cognitively impaired, the participant will not be allowed to continue in the study; however, if the treating neurologist reports that the patient is cognitively competent, the participant may continue the study intervention. If the participant’s SPMSQ score falls in the moderate range (5–7 errors) or if the participant’s neurologist deems them to have significant cognitive impairment, the participant will be instructed to discontinue the study intervention, although data collection will continue. If in the severe range (8–10 errors), the participant will stop all study activities and withdraw from the study because the data is considered unreliable.*Physical impairment*: If a study participant becomes physically impaired due to injury, an adverse event, loss of function due to MS or other diagnoses, they may still participate in the study intervention. Other study procedures such as motor and ocular assessments will be performed dependent on the task and impairment as appropriate. The changes in function will be captured in the extenuating circumstances electronic Case Report Form (eCRF) and adverse event forms in the database.*Pregnancy:* If a study participant becomes pregnant during the study, it will be documented in the REDCap data capture platform on the extenuating circumstances eCRF. The study participant will be instructed to follow the diet that is recommended by the medical team that is providing the participant’s pregnancy-related care. The participant may continue to complete other study procedures.*Treating physician no longer recommends*: If a study participant’s treating physician determines it is no longer in the participant’s best interest to continue with some or all of the study interventions, the participant may remain in the study and complete other study procedures. A participant’s treating physician may direct their patient to discontinue or withdraw from the study intervention if any clinical adverse event (AE), laboratory abnormality, or other medical condition or situation occurs such that continued participation in the study would not be in the best interest of the participant.*Participant discontinues on their own*: If a study participant discontinues part or all of the study intervention on their own, they may remain in the study and complete other study procedures. The study team will record when the study intervention was altered or discontinued via patient report.

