### Statistical methods

#### Statistical methods for primary and secondary outcomes {20a}

Data for this study will be stored electronically using the REDCap platform at the University of Iowa and analyzed in SAS® 9.4. Baseline demographic and clinical measures collected will be summarized and tested for differences between study groups. Categorical measures are displayed as counts (percentages) and use Pearson’s chi-square or Fisher’s exact tests, depending on expected crosstab counts. Continuous measure distributions will be assessed using histograms. Normally distributed measures will be displayed as means (standard deviations) and compared using two-sample t-tests. Non-normally distributed measures will be displayed as medians (interquartile ranges) and compared using the Wilcoxon rank sum test.

The generalized linear mixed modeling (GLMM) [76] framework will be used to test the main and interacting effects of diet and time on the outcome measures of interest while accounting for repeated measures from each participant. The GLMM framework allows for non-normal distributions among the outcome measures. Other potentially important variables (age, sex, BMI, baseline smoking status, baseline alcohol use, walking assistance, years of MS, DMT use, baseline vitamin D, baseline 6-min walk distance) will be considered for inclusion in each model to assess their relationship with the outcome and to determine if they modify the estimates for the diet and time interaction. For each unique model (outcome and predictor set combination), Akaike information criterion (AIC) [77] will be obtained and utilized for model selection. Point estimates, 95% confidence intervals, and p-values of the diet mean changes in outcome measures over visits will be generated for each optimal model. For primary data analysis, data from all participants randomized at baseline will be included in an intention-to-treat analysis. A secondary per-protocol analysis will be used to examine the participants who complete the primary endpoint at 6 months for patient-reported outcomes or had clinical outcome assessments at 24 months. Hypothesis testing of the main effects in each optimal model (according to AIC) will use the Bonferroni correction for multiple comparisons between the three study treatment arms. All analyses will be conducted with two-sided tests (alpha = 0.05) using SAS software version 9.4 (SAS Institute Inc.).

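### The cognitive-impairment rules in section {11b} give conflicting instructions on whether the intervention stops and whether follow-up continues

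*Protocol article*

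**What the plan says.** All the sentences at issue stand in one paragraph of the protocol article, the cognitive-impairment item of section {11b}. In order:

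- At the lower threshold, where "four or more errors are recorded, the study staff will notify the PI to discuss the participant’s cognitive state", staff also write to the treating neurologist.
- A count above four is called a medical stop point, and the neurologist is told of it.
- On a finding of impairment by the neurologist, the rule reads: "If the neurologist determines that the participant is cognitively impaired, the participant will not be allowed to continue in the study".
- For the opposite finding, the second half of that sentence reads: "if the treating neurologist reports that the patient is cognitively competent, the participant may continue the study intervention".
- The next sentence has two alternative triggers, a moderate score of 5–7 errors or a neurologist's view that impairment is significant. Its consequence is that "the participant will be instructed to discontinue the study intervention, although data collection will continue".
- In the severe range (8–10 errors) the participant stops everything and is withdrawn, because the data are regarded as unreliable.

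On the analysis side, section {20a} says that "data from all participants randomized at baseline will be included in an intention-to-treat analysis", and section {20c} leaves missing data to the mixed model.

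**The concern.** The paragraph has to settle two separate things: whether the participant stays on the diet, and whether outcomes go on being collected. For some combinations of score and neurologist finding it answers one of these in two opposite ways.

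Where the conflict concerns the intervention, two participants with the same score and the same finding could be handled differently. Where it concerns follow-up, later outcome values may or may not exist, depending on which sentence staff apply. The trigger is observed cognitive difficulty. Cognition is itself a secondary outcome (SDMT-O, also a component of the MSFC) and plausibly bears on quality of life, so values lost this way may be informatively missing. A mixed model copes with missing values when the missingness can be explained by data in the model. The SPMSQ score and the neurologist's finding are not among the covariates listed in section {20a}, and SDMT-O is measured only at months 0, 3 and 24. A decline between months 3 and 24 may therefore leave no trace in the SDMT-O data if the participant has gone before the last visit.

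**Working it through.** No figure in the plan underlies this point, so the check is logical: apply every sentence of the paragraph to each score range and neurologist finding, and list the instructions that result.

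| SPMSQ errors | Neurologist finding | Intervention | Data collection | Result |
|---|---|---|---|---|
| 4 | none yet | no stop stated | no stop stated | consistent |
| 4 | competent | may go on | no stop stated | consistent |
| 4 | impaired | stops | ended by one sentence; kept by the next if the impairment is significant | conflict on follow-up, conditional |
| 5–7 | none yet | stops | kept | consistent |
| 5–7 | competent | may go on, and must stop | kept | conflict on intervention |
| 5–7 | impaired | stops | ended by one sentence, kept by the next | conflict on follow-up |
| 8–10 | none yet | stops | ended | consistent |
| 8–10 | competent | may go on, and must stop | ended | conflict on intervention |
| 8–10 | impaired | stops | ended by two sentences; kept by a third if the impairment is significant | conflict on follow-up, conditional |

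Five of the nine combinations carry a conflict. Two are conditional on how the neurologist's finding is graded; three are not.

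**Conflict on the intervention.** The moderate-range sentence joins its two triggers with an *or*, so 5–7 errors suffices without any neurologist finding. The sentence that lets a competent participant go on has no score limit. It follows directly on the sentence about more than four errors, so it cannot easily be confined to a participant with exactly four. A participant with 6 errors who is found competent falls under both.

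**Conflict on follow-up.** With 5–7 errors and a finding of impairment, one sentence bars the participant from the study, and the score alone brings in the other sentence, which keeps data collection. This cell does not depend on whether impairment and significant impairment mean the same thing. The 4-error and 8–10-error cells do.

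No other section resolves either conflict. The eligibility section {10} only fixes more than four errors as the exclusion at entry.

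**The case against.** **On follow-up, the wording may simply be loose.** The item sits in a list of reasons for discontinuing the intervention, and the sentence that bars a participant from the study contrasts this with continuing the intervention. On that reading only the intervention is meant, and the next sentence confirms that data collection goes on. This is plausible and makes the second conflict softer than the first. It is not stated, however, and the severe-range sentence of the same paragraph uses withdrawal from the study to mean the end of all activities.

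**Impaired and significantly impaired may be different grades.** The text does not say so. If they were, the lesser finding would end participation while the greater one kept data collection. The 5–7-error cell would conflict regardless.

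**Few people, and late.** This largely stands. Entry excludes more than four errors, and repeating the SPMSQ is at the team's discretion. Section {20a} places the primary endpoint for patient-reported outcomes at 6 months. Recruitment closed on July 22, 2024, so the last month-6 assessment fell around January 2025, before the article appeared on October 27, 2025. Rewording now can affect only later data. Those are not trivial: month 24 for the last participants falls around July 2026, and SDMT-O, MSFC and MRI are due then.

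**Stronger readings that the document does not support.**

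- A reader might infer that affected participants drop out of the intention-to-treat analysis. Section {20a} keeps everyone randomised; what may be lost is outcome data after the event.
- A reader might infer that four or more errors and more than four errors are rival triggers for the neurologist letter. They can be read as two compatible steps: a letter at the lower count, and word to the neurologist when the count passes the stop point.
- A reader might infer that one participant could be kept, stopped or withdrawn. For a fixed score and finding there are usually two competing instructions; all three outcomes appear only when findings are mixed.
- One participant's share of an arm could be computed, but it is not an estimate of bias.

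**Conclusion.** The paragraph is wrong as written. The conflict on the intervention, at 5–7 errors with a finding of competence and likewise at 8–10 errors, is a plain contradiction. The conflict on follow-up after a finding of impairment is a contradiction on the literal text and at least an ambiguity on the kindest reading.

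The effect on the results cannot be sized: the document gives no count of affected participants, and the entry criterion suggests a small one. The possible harm is inconsistent handling of similar participants, and missing later outcomes related to cognition. Nothing in the document shows that this is frequent or differs between arms.

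The conclusion assumes that the published wording is the wording staff follow. If the full protocol already resolves it, only the article needs correcting. How post-discontinuation data enter the model is commonly left to the analysis plan and is not part of this point.

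**What to change.** Reconcile the sentences of the cognitive-impairment item in section {11b} so that every combination of SPMSQ range and neurologist finding leads to exactly one stated outcome for the intervention and exactly one for data collection. A small grid like the one above would do. State whether being barred from the study means the intervention alone or all follow-up, and whether impairment and significant impairment are the same finding. Which outcome belongs in each cell is a clinical decision for the investigators and the IRB.

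For any participant to whom the paragraph has already been applied, record the score, the neurologist's finding, the date and which rule was followed, so that the reason for any missing outcomes is known at analysis.

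Cost: one rewritten paragraph, notification of the IRB and a short log. No new procedures are needed.

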
### Strategies to improve adherence to interventions {11c}

Participants in the MPE diet group will be considered adherent to their diet if DHQ-III survey indicate that they consumed within 20% of recommendations for key intervention diet components (≥ 5 cup equivalent servings of total fruit and vegetables). Adherence to the TROO ketogenic diet will be determined by participants achieving a ketogenic ratio (KR) value of > 1.5 on DHQ-III surveys or by being in nutritional ketosis in 80% of the ketone readings throughout the trial. KR value ≥ 1.5 is considered the minimum threshold to predict a ketogenic diet and will be calculated as follows: (0.9*grams fat + 0.46*grams protein) divided by (0.1*grams fat + 0.58*grams protein + grams total carbohydrate – grams total fiber). In the event the study intervention becomes too restrictive or difficult for the study participant to maintain, the study team has created diet adherence guidelines to give participants options to ease the burden of the study intervention and prevent study discontinuation (Table 2). One of the senior investigators, who has extensive experience conducting long-term, randomized controlled dietary intervention trials, was unblinded and responsible for monitoring and supporting participant adherence to the dietary protocols.

**Table 2 Tab2:**
[figure not shown]
Intervention diets adherence guideline

### Relevant concomitant care permitted or prohibited during the trial {11d}

We ask the participants not to start any new supplements, over-the-counter medications, or new MS self-care interventions (e.g., sauna, cold plunges, yoga) during the study unless directed by their physician. In addition, participants are to report any concomitant medications including prescription medications, therapies for treating adverse events, MS relapses, over-the-counter medications, and dietary supplements.

### Provisions for post-trial care {30}

The participants randomized to usual care group will be offered the opportunity to elect to receive educational resources for one (but not both) of the intervention diets, MPE or TROO ketogenic, at their month 24 (end of study) visit.

### Outcomes {12}

#### Primary outcome

The primary outcome of this study is changes in mental and physical QoL scores over time in the intervention groups compared to the control group assessed using the MS Quality of life 54 (MSQoL-54) questionnaire, which is a validated 54-item questionnaire of MS-specific physical- and mental health-related QoL.

#### Secondary outcomes

Secondary outcomes include objective disease course (MRI brain imaging), ocular structure and function, perceived fatigue, mood, self-reported disability status, motor function, and cognitive function. Table 3 summarizes the primary and secondary outcomes and measures.

**Table 3 Tab3:**
[figure not shown]
Study outcomes

#### Exploratory outcomes

Exploratory outcomes include identifying potential mechanisms via single voxel magnetic resonance spectroscopy (MRS) in frontal lobe white matter to identify brain metabolite changes over time.

### Participant timeline {13}

The protocol was prepared according to the Standard Protocol Items: Recommendations for Interventional Trials (SPIRIT) guidelines [34] (Fig. 1; and Additional file 3: SPIRIT checklist). Figure 2 shows the EDQ-MS study flow diagram.

**Fig. 1 Fig1:**
[figure not shown]
Standard Protocol Items: Recommendation for Interventional Trials (SPIRIT): the schedule of enrollment, interventions, and assessments

**Fig. 2 Fig2:**
[figure not shown]
Efficacy of Diet on Quality of Life in Multiple Sclerosis (EDQ-MS) study flow diagram

### Sample size {14}

Sample sizes required to achieve 80% power for testing between-treatment changes over time were calculated for each measure using summary statistics at baseline and 6-months from our previous randomized parallel arm trial comparing the LSF and MPE diets.

Using a group sample size of 36 and an alpha of 0.05, power and estimates for mean difference within and between groups are shown in Table 4. To ensure adequate sample size at the primary endpoint of the study, we will enroll enough participants to cover a 33% attrition rate in each group, giving a final target enrollment sample size of *n* = 54 per group.

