### Assignment of interventions: allocation

#### Sequence generation {16a}

Study participants will be randomized and evenly allocated at a 1:1:1 ratio to one of the following groups: MPE diet, or TROO ketogenic diet, or usual care control with DGA educational material, to remove bias from any staff performing study assessments responsible for the primary outcomes.

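### The 80% power is stated at an unadjusted alpha of 0.05, while the analysis plans a Bonferroni correction between the three arms, so the power statement and the decision rule use different alphas

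*Protocol article*

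**What the plan says.** **Sample size {14}.** The target is given as: "Sample sizes required to achieve 80% power for testing between-treatment changes over time were calculated for each measure". The section then fixes one group size for all measures and refers to Table 4 for the results by measure: "Using a group sample size of 36 and an alpha of 0.05, power and estimates for mean difference within and between groups". Allowing for 33% attrition, it reaches 54 per group. No multiplicity adjustment is mentioned.

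**Statistical methods {20a}.** The overall level is set by "All analyses will be conducted with two-sided tests (alpha = 0.05". The correction is introduced with "Hypothesis testing of the main effects in each optimal model (according to AIC" and continues that it "will use the Bonferroni correction for multiple comparisons between the three study treatment arms". The number of comparisons is not stated.

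**Primary outcome.** The outcome is "changes in mental and physical QoL scores over time in the intervention groups compared to the control group", that is, each of two diets against control.

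**Sequence generation {16a}.** Participants are "evenly allocated at a 1:1:1 ratio", so the arms are equal in size.

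**The concern.** The two sections set different thresholds for what may be the same test. If each comparison is judged at 0.05 divided by two or three, power computed at 0.05 is not the power of that test. It is too high, whatever value Table 4 shows.

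The wording adds a second problem. The test that was powered is the difference between arms in change over time, which in the planned mixed model is the diet-by-time contrast. The Bonferroni sentence is attached to main effects. Read literally, the correction might not reach the powered contrast at all, and the article would then state no multiplicity control for that contrast. Either way, the two sections need to be brought together.

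At stake is how the quality-of-life result is read. Recruitment closed in July 2024, so the power statement can no longer guide enrolment, but it will frame the results. If the trial is described as having 80% power and the tests are stricter than that description assumes, a non-significant result will look like stronger evidence of no effect than it is.

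**Working it through.** **Inputs**

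- Evaluable per group: 36; alpha: 0.05; target power: 80% (Sample size {14}).
- Two-sided tests and a Bonferroni correction between three arms (Statistical methods {20a}).
- Equal allocation (Sequence generation {16a}).
- Number of comparisons, k: not stated. Taken as k = 2 (each diet against control, following the primary objective) or k = 3 (all pairs of arms).
- Difference, SD and power by measure: in Table 4, not visible. Power at 0.05 is therefore an assumption, set at 80% and then varied.

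**Step 1. The plan's own enrolment figure.** 36 / (1 − 0.33) = 53.7, rounded up to 54; 3 × 54 = 162. This reproduces. The 80% itself cannot be reproduced without Table 4.

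**Step 2. The effect implied by 80% power.** For a two-sample t test with n per group, the degrees of freedom are 2n − 2 and the noncentrality is d × √(n/2). Solving for 80% power at n = 36 and two-sided 0.05 gives d = 0.67. The normal approximation gives (1.960 + 0.842) × √(2/36) = 0.66.

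**Step 3. Power for that same effect at the corrected alpha.** As a normal check, power = Φ(1.960 + 0.842 − z), where z is the two-sided critical value at 0.05/k.

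| k | Alpha per comparison | z | Power, normal | Power, noncentral t |
|---|---|---|---|---|
| 1 | 0.05 | 1.960 | 80.0% | 80.0% |
| 2 | 0.025 | 2.241 | 71.2% | 70.8% |
| 3 | 0.0167 | 2.394 | 65.8% | 65.1% |

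**Step 4. Other starting values.** With a common group size, power will generally differ from measure to measure. Noncentral t, 36 per group:

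| Power at 0.05 | k = 2 | k = 3 |
|---|---|---|
| 80% | 71% | 65% |
| 85% | 77% | 72% |
| 90% | 84% | 80% |
| 95% | 91% | 88% |

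To keep 80% after the correction, a measure needs about 87% at 0.05 when k = 2, or about 90% when k = 3.

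**Step 5. Detectable difference with 80% power, 36 per group.** 0.67 SD at 0.05; 0.74 SD at 0.025; 0.78 SD at 0.0167.

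**Step 6. Evaluable per arm that restores 80% for d = 0.67.** 44 when k = 2 and 49 when k = 3. Out of 54 per arm, these correspond to attrition of at most (54 − 44)/54 = 18.5% and (54 − 49)/54 = 9.3%, against the 33% allowed for.

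**The case against.** The strongest reply is that the size of the loss rests on a table that cannot be seen. The text fixes 36 per group and leaves power by measure to Table 4. If the two MSQoL-54 scores have 90% power there, about 80% remains even after a three-way correction. This stands, so the loss can only be given conditionally.

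Second, the statistical methods section itself writes alpha of 0.05 beside the Bonferroni sentence, as the nominal level before division. The sample size section might use the figure in the same way, with a note on adjustment in Table 4. That is possible, but nothing in the visible text says so. A reader of the sample size section will take 0.05 as the alpha used.

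Third, the number of comparisons is open. The correction refers to all three arms, which suggests three pairs; the objective and primary outcome point to two. Both readings lose power relative to 0.05, and neither can be ruled out.

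Fourth, a two-sample t test on 36 per arm is not the planned analysis. The plan is a repeated-measures mixed model on all randomised participants, and 36 is the number left if the full 33% is lost. The primary endpoint for patient-reported outcomes is at 6 months, where retention may be better. This stands as a limit on the absolute figures. It does not remove the mismatch of alphas.

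Two stronger readings are tempting. A reader might infer that the trial has 65% power instead of 80%. The document does not support that as a fact, because it needs both exactly 80% in Table 4 and three comparisons. A reader might also divide alpha further for the two primary scores, physical and mental. The Bonferroni sentence corrects over arms only, so those smaller alphas have no basis in the text.

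**Conclusion.** The point holds as an inconsistency within the protocol article: the power statement uses an unadjusted 0.05, and the decision rule uses a Bonferroni-corrected level. Any power computed at 0.05 is too favourable for the corrected test.

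The size is conditional. If power is exactly 80% at two-sided 0.05 with 36 evaluable per group, it is about 71% for two comparisons and about 65% for three, under a two-sample t approximation. An effect of the planned size would then be missed in 29% to 35% of trials instead of 20%. If power at 0.05 is 90%, about 84% or 80% remains and there is no material shortfall against the target. Retention better than planned would also narrow the gap. Whether the correction applies to the powered contrast is unclear from the wording and has to be settled before any one figure can be quoted. The attrition arithmetic is correct.

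**What to change.** 1. In Statistical methods {20a}, state how many confirmatory comparisons there are: two (each diet against control) or three (all pairs).
2. In the same place, say that the Bonferroni correction applies to the diet-by-time contrast that was powered, not only to main effects.
3. Recompute Table 4 and the sample size sentence at the resulting alpha (0.025 or 0.0167). Restate either the power for each measure or the detectable difference. For a measure now credited with 80%, that means about 71% or 65% power, or 0.74 or 0.78 SD in place of 0.67 SD.
4. Add that 44 evaluable per arm (two comparisons) or 49 (three), out of the 54 per arm targeted, would restore 80% for the 0.67 SD effect.

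The cost is a few sentences and one table, which can be done before the final analysis. No extra enrolment is called for. The only downside is that the stated power becomes less favourable.
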